## Abstract

**Background:**

Nonpharmacological secondary prevention of coronary heart disease is considered a safe and effective measure to substantially reduce mortality. Despite the effectiveness of lifestyle changes, the compliance rate of patients is very low mainly due to psychosocial barriers. Psychotherapeutic approaches that address how persons think about themselves and their behaviors appear to have a significant potential for improving health behavior.

**Methods/design:**

Against this background, our study aims to examine the feasibility and effects of a Psychodynamic Motivation and Training program (PMT) as compared to one session of advice in exercise training (EX) and treatment as usual (TAU). For that purpose, 90 patients with stable coronary heart disease and a physically inactive lifestyle will be randomly assigned to the three groups (each with n = 30). The primary outcome is the change in the individual anaerobic threshold as determined by spiroergometry from baseline to six month follow-up. Secondary endpoints include change in endothelial function, biomarkers of inflammation and oxidative stress, quality of life, symptoms of fatigue, illness perception and feasibility of the treatment approach. We hypothesize that physical fitness will improve more in PMT than in EX and TAU, with PMT and EX more than TAU, and that the effects will be more pronounced for participants with current mental or psychosocial distress.

**Discussion:**

The results of the study will help to determine the effectiveness of a psychodynamic lifestyle change approach and to identify measures for designing specifically tailored interventions to improve compliance with cardiovascular prevention.

**Trial registration:**

ClinicalTrials.gov Identifier: NCT01445808

## Background

Coronary heart disease (CHD) is the leading cause of disability and death in Western societies. The prognosis of established CHD is strongly influenced by lifestyle factors such as smoking, unhealthy diet and physical inactivity. Among those lifestyle risk factors, physical inactivity is the most prevalent. In Europe, less than 50% of the population is involved in regular aerobic leisure-time, and/or occupational physical activity [1]. Regular physical activity and aerobic exercise strongly reduce the risk of fatal and non-fatal coronary events in patients with CHD, buffer psychosocial distress and improve quality of life and symptoms of depression [2-5]. Therefore, targeting physical inactivity is considered a very important non-pharmacological tool for secondary cardiovascular prevention. Accordingly, for persons with stable coronary heart disease the European Heart Association strongly recommends ‘moderate-to-vigorous intensity aerobic exercise training ≥ three times a week and 30 minutes per session’; and ‘sedentary patients should be strongly encouraged to start light-intensity exercise … after adequate exercise-related risk stratification’ [1].

The overall risk reduction by at least three months of aerobic exercise programs is around 30%. The positive effects of aerobic exercise result from an improved ability to use oxygen to derive energy for work [1], decreased myocardial oxygen demands, improvement of myocardial perfusion, antithrombotic effects, anti-inflammatory effects and anti-arrhythmic effects by favorable modulation of autonomic balance and improvement of endothelial function [1,2].

Despite its favorable effects, implementation of physical activity recommendations has been proven highly problematic in daily life [6]. Psychological and socio-economic factors have been identified as important barriers [7-9]: economic disadvantage, overwork, family duties, feeling physically restricted towards or fearful of exercise, lacking knowledge regarding exercise, negative perceptions towards health, lack of motivation and depression.

Psychotherapeutic strategies have been proven as crucial components of lifestyle interventions, because the interventions need to address how persons think about themselves, their behaviors, and life circumstances [10]. The more these essential components were addressed, the more effective the interventions became [10]. The following techniques were especially important [10]: clarification of the goals and motivation of the individual, providing feedback and reinforcement for progress toward goal achievement, establishing peer-based support, strengthening self-monitoring and self-efficacy. Of note, the authors of the scientific statement of the American Heart Association [10] labeled the above strategies as cognitive-behavioral, however, considering current generic models of psychotherapeutic processes these are better described as general psychotherapeutic strategies [11].

Interestingly, the term ‘lifestyle’ was originally coined by Alfred Adler (1870 to 1937), an Austrian medical doctor, psychotherapist and founder of the psychodynamic school of ‘Individual Psychology’. The ‘style of life’ refers to how individuals live their life and how they handle problems and interpersonal relations [12]. The individual lifestyle is determined early in childhood by the individuals’ interpersonal and social experiences. Health behaviors like physical activity, smoking and dietary habits are essential components of the individual lifestyle. The modern use of ‘lifestyle’ sometimes trivializes health behavior as it suggests that an individuals’ lifestyle might be the result of the individuals’ conscious decisions like choosing to buy a certain brand of chocolate. However, this view neglects the importance of biological, social, developmental, environmental, and psychological factors contributing to the individual’s lifestyle [13-16]. Briefly, the effectiveness of psychotherapeutic techniques as compared to mere provision of information demonstrates that mental factors play a significant role for health behavior. There is already consensus that this is true for smoking, which is regarded as an addictive disorder in line with alcohol abuse or alcohol dependence. In similar ways, this may be also true to some degree for eating behavior or physical activity.

The present study aimed to investigate the effectiveness of a psychodynamic approach to health behavior for secondary prevention of cardiovascular disease. To our knowledge, up to date no psychodynamic treatment studies have been explicitly targeting the improvement of physical activity, respectively lifestyle improvement. However, stronger recognition of lifestyle in psychotherapy is an urgent need. Firstly, the detrimental effects of depression on the development and outcome of coronary heart disease are largely mediated by insufficient physical activity and smoking [2,17-19]. Secondly, poor health behavior is suggested to impair treatment outcome of mental disorder itself [19]. Therefore, targeting lifestyle change is considered to be a crucial component of effective treatments [20]. According to our knowledge, the ongoing stepwise psychotherapy intervention for reducing risk in coronary artery disease (SPIRR-CAD, [21]) is the only psychotherapy study, formulating explicitly health behavior as a treatment focus. SPIRR-CAD was designed to treat depression in patients with coronary heart disease. The focus of the psychodynamic group psychotherapy also included health behavior: there is one session of psychoeducation about modifiable cardiovascular risk factors and each session of the group psychotherapy begins with a brief statement of the patient about his feelings and health behavior.

As psychodynamic psychotherapy is widely-used in Western societies, it is desirable to develop psychodynamic interventions suitable for lifestyle improvement. Especially in Germany, family doctors and other specialists are formally trained in the low-threshold provision of basic mental health care and many have also been trained in psychotherapy for medically ill persons according to psychodynamic principles.

This study aims to determine the feasibility of the new treatment approach, to identify possible effects and effective components for designing specifically tailored interventions to improve compliance with cardiovascular prevention, respectively lifestyle change, that may be worth following up in subsequent larger trials.

## Methods/design

### Study center

The multidisciplinary single center randomized trial with three parallel groups is carried out in collaboration among the Departments of Cardiology, Psychosomatic Medicine and Psychotherapy and Sports Medicine at the University Medical Center of the University of Mainz.

### Participants

Patients are eligible to participate if they fulfill the following criteria: age between 18 to 75 years, stable coronary heart disease determined by percutaneous coronary intervention and low physical activity.

Patients are recruited from the Department of Cardiology of the University Medical Center Mainz and private practices of general practitioners and cardiologists, by research advertisement in the local newspapers and announcements on the webpage of the University Medical Center. Further, patients who were hospitalized for percutaneous coronary intervention during the last ten years are actively approached with an information letter. Once a patient articulates his interest in participation, he signs an informed consent allowing the inspection of any medical records and screening for physical activity. The individuals’ medical records are reviewed for the inclusion and exclusion criteria by a research assistant and a medical doctor. Low physical activity was defined as less than 15 to 20 minutes of at least moderate exercise training per week during the last month according to the definition of the Heart and Soul Study [17]. This criterion was a strong predictor of mortality in post-myocardial patients [17]. After the review of the medical records, the patient is contacted, usually by phone, and interviewed for inclusion and exclusion criteria. Further, he receives information about the procedures and aims of the study. If the patient is eligible and willing to participate, he/she is invited to the study center for further information. After discussion of the study procedures, he/she is asked to sign the informed consent for trial participation. Participating patients are paid an allowance of €25 for the baseline assessment and €75 for the follow-up assessment.

Table 1 lists the inclusion and exclusion criteria. Inclusion and exclusion criteria were selected based on the following considerations: firstly, in order to ensure a valid diagnosis of coronary heart disease, a percutaneous coronary intervention was required. Secondly, in order to keep the threshold for participation low. Thirdly, in order to be able to analyze biological outcome parameters such as inflammation, endothelial function and anaerobic threshold. For the latter purposes, the participants should not be treated with insulin or systemic immunosuppressant drugs. Changes in medication with beta-blockers, statins and drugs acting on the renin-angiotensin axis in the last two weeks before each planned visit were not allowed (that is, visits were rescheduled).

**Table 1 T1:** Inclusion and exclusion criteria

	
Inclusion criteria:	
1.	Stable coronary heart disease with CCS functional classification of angina class I to III
2.	Low self-rated physical activity
3.	Condition after percutaneous coronary intervention > 4 weeks until < 26 weeks or > 52 weeks after index percutaneous coronary intervention
4.	Residence < 50 km radius of the study center (city of Mainz)
5.	If treatment with beta blockers or ivabradine then stable > 4 weeks
Exclusion criteria:	
1.	Acute coronary syndrome or myocardial infarction < 8 weeks
2.	Coronary stenosis of the dominant vessel > 25% or high grade stenosis of the left coronary artery
3.	Heart failure with left ventricular ejection fraction < 40%
4.	NYHA III to IV
5.	Severe heart valve disorder
6.	Insulin dependent diabetes
7.	Orthopedic or other disorders, which preclude regular physical activity
8.	Coronary artery bypass surgery < 6 months before index PCI
9.	Severe obesity (BMI ≥ 40)
10.	Need for systemic immunosuppression with cortisone or methotrexate
11.	Kidney failure with need for dialysis
12.	Intake of nitrates < 12 hours

*CCS* severity of angina according to the Canadian Cardiovascular Society, *NYHA* symptoms of heart failure according to the New York Heart Association, *PCI* percutaneous coronary intervention.

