### Psychometric questionnaires

Quality of life is assessed by the EQ-5D™ (EuroQuol Group, Rotterdam, Netherlands) [34]. The EQ-5D™ captures problems pertaining to usual activities and anxiety/depression dimensions, and the respondent’s own assessment of their health status on a visual scale from 0 (worst imaginable health) to 100 (best imaginable health). Coronary artery disease related quality of life is measured with the Seattle Angina Questionnaire (SAQ) [35].

Feelings of vital exhaustion are assessed by the Maastricht Questionnaire [36] and symptoms of fatigue by the MFI Multidimensional Fatigue Inventory (MFI) [37].

Insomnia symptoms were measured by the Jenkins sleep questionnaire [38], covering difficulties initiating and maintaining sleep as well as non-restorative sleep. Occurrence of sleep disturbances is rated for the previous four weeks from: not at all (1), 1 to 3 days (2), 4 to 7 days (3), 8 to 14 days (4), 15 to 21 days (5) to 22 to 28 days (6).

The cognitive and emotional representations of the coronary heart disease are measured by the brief Illness Perception Questionnaire (IPQ) [39]. Changing patients’ illness perceptions may improve outcome in coronary heart disease [40].

Self-rated habitual physical activity was measured by the Habitual Physical Activity Questionnaire [41] and the one item screener from the Heart and Soul Study [17]: ‘Which of the following statements best describes how physically active you have been during the last month, that is, done activities such as 15 to 20 minutes of brisk walking, swimming, general conditioning, or recreational sports?’ Participants chose from one of the following six categories: not at all active, a little active (1 to 2 times per month), fairly active (3 to 4 times per month), quite active (1 to 2 times per week), very active (3 to 4 times per week), or extremely active (≥ 5 times per week). Being ‘not at all’ or ‘a little’ active is considered as physically inactive.

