### Randomization

The participants are randomized to three groups with n = 30 patients each. A computer program randomly assigned numbers from 1 to 90 to three sets representing the three groups. The numbers were hidden in closed envelopes. For each new participant an envelope was opened and the participant was allocated accordingly.

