### Statistical methods

Categorical variables are presented as frequencies and percentages (n,%), continuous variables as means and standard deviations (mean ± standard deviation), or medians and quartiles for variables with skewed distributions (median (25th quartile, 75th quartile). Baseline characteristics of the three treatment groups will be compared with respect to age, sex, socioeconomic status, partnership, cardiovascular risk-factors (for example, smoking, obesity), comorbidity, variables characterizing patients with coronary heart disease (for example, medication) and outcome parameters.

Primary and secondary endpoints will be analyzed according to the intention-to-treat principle. Change from baseline to follow-up will be analyzed by analysis of covariance adjusting for baseline measurement of the respective outcome. Doing so, separate contrast are specified for comparing PMT with EX and TAU, respectively. Cohen‘s effect size will be calculated. In order to determine whether the effect of PMT is modified by presence of significant mental distress and psychosocial stressors at baseline, a test for interaction will be performed. Exposure to significant mental distress and psychosocial stressors will be defined by at least one of the following baseline criteria: PHQ-2 ≥ 2, GAD-2 ≥ 3, sleep disturbances (according to item #3 of the PHQ-9 ≥ ‘more than half the days’), and common psychosocial stressors according to the PHQ module (‘being bothered a lot’ by ‘difficulties with husband/wife, partner/lover or boyfriend/girlfriend’, or ‘stress of taking care of children, parents, or other family members’, or ‘stress at work outside of the home or at school’, or ‘having no one to turn to when you have a problem’). All analyses will be conducted on a two-sided level of significance with *P* < 0.05.

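### Entry mixes recent and remote PCI patients and judges inactivity over one month only; PCI phase should be a prespecified covariate in the ANCOVA

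*Protocol article*

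**What the plan says.** The abstract describes the target group as "90 patients with stable coronary heart disease and a physically inactive lifestyle". Under Participants, low activity means "less than 15 to 20 minutes of at least moderate exercise training per week during the last month". The one-item screener under Psychometric questionnaires uses the same window, asking which statement "best describes how physically active you have been during the last month". No instrument described in the article asks about activity before the PCI.

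Table 1, inclusion criterion 3, reads "Condition after percutaneous coronary intervention > 4 weeks until < 26 weeks or > 52 weeks after index percutaneous coronary intervention". This gives two separated windows, with 26 to 52 weeks left out. Table 1 also requires "Stable coronary heart disease with CCS functional classification of angina class I to III" and excludes "Acute coronary syndrome or myocardial infarction < 8 weeks".

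Under Randomization, "A computer program randomly assigned numbers from 1 to 90 to three sets representing the three groups"; no strata are described. Under Statistical methods, "Change from baseline to follow-up will be analyzed by analysis of covariance adjusting for baseline measurement of the respective outcome". The only effect modifier to be tested is mental distress and psychosocial stressors. The Discussion considers further adjustment for blood pressure and control for psychopharmacotherapy, but does not mention time since PCI.

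**The concern.** A patient screened five weeks after PCI is asked about a month that lies almost wholly after the procedure. A person who is usually active but was resting in those weeks can meet the criterion, and so can a person who has been inactive for years. The first may regain fitness over six months without help; the second may not. If so, PCI phase predicts the primary outcome, change in power at the individual anaerobic threshold.

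A prognostic factor left out of both the allocation and the model has two related consequences. The spread between phases stays in the error term, and in arms of 30 the recent-PCI share can differ by chance, moving an individual estimate up or down. At stake is some precision in a trial planned with power close to 0.80 for each of its two contrasts. Eligibility already requires the time since the index PCI, so the information to prevent this is on file.

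**Working it through.** **Inputs from the article (Sample size calculation).** n = 30 per arm; two-sided level 0.025 per comparison (Bonferroni, two comparisons); standardised effect 0.82; power 0.80; SD of change 17 W; absolute effect 14 W.

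**Step 1: the plan's own figure.** Two-sample t-test, noncentral t with 58 degrees of freedom, noncentrality 0.82 × √(30/2). Power is 0.807, against 0.80 stated. The absolute effect is 0.82 × 17 = 13.9 W, stated as 14 W. The planning figures reproduce.

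**Step 2: expected contrast under shared recovery.** Let p be the share of recent-PCI patients and r their extra spontaneous gain, the same in every arm. With a treatment effect of 14 W:

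- expected change with PMT = 14 + p·r (plus a common constant)
- expected change with TAU = p·r (plus the same constant)
- difference = 14 W, whatever p and r are

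Shared recovery therefore cancels in the randomised comparison.

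**Step 3: residual variance.** With phase left out, the variance is multiplied by 1 + p(1 − p)r², with r in units of the within-phase SD, taken as 17 W. The article gives neither p nor r. For p = 0.5 and r = 0.5 (8.5 W):

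- factor = 1 + 0.25 × 0.25 = 1.0625
- effective effect size = 0.82/√1.0625 = 0.796
- power = 0.780

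The same calculation over a range of assumed values gives these powers:

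| p | r = 0.25 SD | r = 0.5 SD | r = 1 SD |
|---|---|---|---|
| 0.10 | 0.80 | 0.80 | 0.77 |
| 0.25 | 0.80 | 0.79 | 0.73 |
| 0.50 | 0.80 | 0.78 | 0.70 |

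**Step 4: chance imbalance.** SD of the difference in recent-PCI share between two arms = √(2 × p(1 − p)/30). At p = 0.5 this is √(0.5/30) = 0.129, or about 13 percentage points. At p = 0.10 it is 0.077. With p = 0.5 and r = 8.5 W, an imbalance of 1.96 SD shifts an unadjusted contrast by 1.96 × 0.129 × 8.5 = 2.1 W, in either direction. Steps 3 and 4 describe the same source of error, before and after the allocation is known, so they should not be added together.

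**Step 5: price of the covariate.** Going from 58 to 57 error degrees of freedom at d = 0.82 moves power from 0.8065 to 0.8062, a loss below 0.001.

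**The case against.** The strongest reply is that nothing here is an error. The trial is randomised with a concurrent TAU arm, so recovery is spread over all arms. An unstratified list for 90 patients is acceptable. Adjusting for the baseline threshold may already absorb part of any temporary deconditioning, and further covariates may stand in an analysis plan not shown. The affected group is also narrow: disease must be stable and an acute event within 8 weeks excludes. The look-back month reaches the first four weeks after PCI only for patients screened at about weeks 4 to 8. As an illustration, assume half the patients are recent-PCI and enter evenly over weeks 4 to 26. That group is then 0.5 × 4/22, about 9% of the trial, and only those previously active would be misclassified. Finally, the two-window covariate is coarse, since it codes a patient at week 20 like one at week 5.

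Most of this stands and limits the point to a modest gain in precision. It does not remove it: the article names its primary covariate and the further adjustments it contemplates, and time since PCI is not among them, although Table 1 itself creates the two groups.

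A reader might go further and infer that convalescent patients dilute the PMT contrasts. That needs a second premise, that PMT does less for them. If a quarter of the patients gained only half the effect, the contrast would be 12.3 W and power 0.67 to 0.68; with no effect in that quarter, 10.5 W and 0.51 to 0.52. The article supports neither the premise nor such a share. It lists fear of exercise and feeling physically restricted among the barriers (Background), and describes patients who become anxious on learning that angioplasty is not a cure (Psychodynamic motivation and training program). Patients who became inactive around the procedure may be just those PMT is meant to reach.

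**Conclusion.** The point holds as an improvement in precision, not as a bias. The article judges inactivity over one month, admits patients from just over 4 weeks after PCI in two separated windows, and uses time since PCI in neither the allocation nor the model it describes. The expected PMT versus EX and PMT versus TAU contrasts are unaffected by recovery common to all arms.

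The size is modest: about 3 points of power per contrast (0.81 to 0.78), and an SD of about 13 percentage points for the difference in recent-PCI share between two arms. These figures assume that half the patients are recent-PCI and that phase shifts spontaneous change by 0.5 SD. With a smaller share or a smaller shift the loss is about 1 to 2 points; with a full SD at p = 0.5 it is about 10. If phase does not predict change, nothing is lost by leaving it out. Diluted contrasts remain possible but are not shown by the document.

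**What to change.** In Statistical methods, prespecify PCI phase (more than 4 to less than 26 weeks versus more than 52 weeks, from the index PCI date) as a fixed covariate in the analysis of covariance for the primary and secondary endpoints, alongside the baseline value of the outcome. Settle this before the follow-up data are analysed.

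The cost is one degree of freedom and no new data collection, because eligibility already depends on this date. The downside is little or no gain if phase turns out not to be prognostic.

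Do not change the eligibility rule. Recruitment is under way, so requiring low activity before the PCI as well would mix two entry definitions, rely on recall over several months, and might exclude patients whom PMT is intended to help.
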